**Discussion:**

This is the study design of a single center, prospective, randomized controlled trial to investigate whether guided ventriculostomy is superior to the standard freehand technique. One strength of this study is the prospective, randomized, interventional type of study testing a new easy-to-handle guided versus freehand ventricular catheter placement. A second strength of this study is that the power calculation is based on catheter accuracy using an available grading system for catheter tip location, and is calculated with the use of recent study results of our own population, supported by data from prominent studies.

**Trial registration:**

Clinicaltrials.gov identifier: NCT02048553 (registered on 28 January 2014).

## Background

Ventriculostomy is a common procedure in neurosurgery and accurate placement of the ventricular catheter is one of the most important variables in the longevity of shunt survival
[1, 2]. Despite this large volume of patients and technological advances, failure rates due to proximal catheter obstruction with the freehand technique remain high (12%, 32%,36%, 38%, and 45% in studies
[3–7], respectively. Optimal placement in the ipsilateral anterior horn of the lateral ventricle just anterior to the foramen of Monro depends on accurate placement of the catheter tip in the ventricle, away from the choroid plexus and injured ependyma
[8], and on proper insertion trajectory and catheter length
[9]. In a retrospective study in 90 patients using surface anatomical landmarks alone, only 56% of the catheter tips were in the ipsilateral lateral ventricle, 7% were in the contralateral lateral ventricle, 8% were in the third ventricle, 6% were within the interhemispheric fissure, and 22% were within extraventricular spaces
[10].

The high rate of malplacements led to a search for improved methods that might result in significant patient benefits. In the last 25 years, techniques using a guide
[11], calculating optimal catheter lengths combining computed tomography (CT)
[12], and stereotactic coordinate-guided freehand methods based on ventricular landmarks
[9, 13] have been developed. This was followed by the more sophisticated methods of the ultrasound transducer
[14–16], neuronavigation, and endoscopic guidance
[17].

A very recent study comparing the accuracy of ventricular catheter placement using the freehand technique, ultrasonic guidance, and stereotactic neuronavigation identified the use of the freehand technique as the only risk factor for inaccurate placement
[7]. Current available image-guided techniques for catheter placements can be time consuming
[14, 18], expensive, and may need a larger burr hole
[19]. The development of an easy-to-use, portable, image-guided system could reduce the need for multiple passes and improve the rate of accurate catheter placement
[16]. Recently, a smartphone-assisted guide was tested in 35 patients with no ventricular catheter failure occurring during the follow-up period
[20].

As there is a need to improve current practices in the placement of ventricular catheters, this study aims to compare prospectively and in a randomized controlled manner the accuracy of the freehand pass technique versus a portable adjustable guiding device for ventriculostomy catheter placement.

## Methods/Design

This is a single center, prospective, randomized trial with a blinded endpoint (ventricular catheter tip location) assessment. Adult patients with the indication for ventriculostomy, as proven by CT, will be randomly assigned to the treatment group or the control group. For patients in the treatment group, a ventriculostomy will be performed using an adjustable guiding device and DICOM (Digital Imaging and Communications in Medicine) image-reading software assistance (for example, using a mini-tablet) based on preoperative CT imaging.

### Design and setting

The guided versus freehand ventriculostomy (VENTRI-GUIDE) study will be performed as a -two-arm, single center, randomized controlled trial to compare an intervention group using a guided placement of a ventricular catheter to a control group receiving standard (freehand) ventriculostomy with a blinded endpoint (catheter tip location) assessment (Figure 
1).

**Figure 1 Fig1:**
[figure not shown]
**Study design.**

The present study is in compliance with the Helsinki Declaration. The protocol of this study was approved by the Ethics Committee on Human Research of the Medical Faculty of the University of Geneva, Switzerland (reference number: CER 13–175). At the planned start of the study (1 February 2014), the study center will start randomization.

Adults with indication for a ventricular drainage are eligible for trial participation and are recruited for this study. The choice of the method of the respective operative procedure is via randomization. All other surgical and medical treatment is performed according to local guidelines and standard operating procedures.

### Subject inclusion criteria

The inclusion criteria for this study are patients aged 18 years or older with an indication for a ventricular drainage (such as hydrocephalus, slit ventricles, or pseudotumor cerebri).

### Subject exclusion criteria

Patients who meet any of the following criteria will be excluded from the study: pregnancy, concurrent participation in another interventional trial (participation in an observational trial is not an exclusion criteria), or if a frontal burr hole is not available.

#### Randomization

The randomization process will start as soon as possible after consent to the study has been obtained. Any patient meeting the inclusion criteria and not violating the exclusion criteria may participate in the VENTRI-GUIDE study and be randomized to either a guided or freehand ventriculostomy. Online randomization will be performed by the treating physician in the study center using permuted blocks, to ensure an equal number of patients in both study arms.

### Surgical technique for guided group intervention

The study is conducted in the neurosurgical department of a Swiss single center university hospital in adult patients with an indication for a ventricular drainage (such as hydrocephalus, slit ventricles, or pseudotumor cerebri). Data management and monitoring will be performed by the Geneva study center and statistical analysis by one of the authors (NS).

For guidance, an easy-to-handle instrument, assisted by DICOM image-reading software (for example, mini-I-pad™ application software; Apple™ Inc(Apple Inc., Cupertino, California, United States ), is used in order to achieve precise placement of ventricular catheters on an every-case basis. The catheter may be placed for external drainage or internal (ventriculoperitoneal) shunting.

For patients in the guided group, catheter placement is performed in the operating theatre during anesthesia under routine sterile conditions and antibiotic prophylaxis. The smartphone-assisted technique used for guided placing of a ventricular catheter through a burr hole has been previously described in detail
[20]. The only difference in this study is the use of an easy-to-use portable DICOM image-reading software assistance (for example, using a mini-tablet) available for all neurosurgeons instead of a smartphone. In brief, the patient is positioned and draped in typical sterile fashion for a ventriculostomy (if necessary, the operation field is enlarged for shunt placement. Then, a frontal burr hole is made using a standard adult perforator.

The guiding instrument consists of a base with three pins to be rigidly placed on the bone surface over the burr hole. A semicircular guide rod (Aesculap AG, Tuttlingen, Germany is mounted to the base in which an angle scale is engraved. Within the guide rod, a tube can be individually adjusted in one orientation at different angulations with a range from -60° to 60°. Different tubes are designed with inner diameters of 2, 2.5, and 3 mm in order to guide catheters at different sizes. At the respective angle adjustment, the tube is fixed to the guide rod by a mounting screw. The base is opened at one side to enable the view or insertion of any instrument towards the lower opening of the tube. The guiding tool is positioned parallel to the midline along the engraved linear markings on the base of the instrument. Thereby, a rectangular insertion towards the sagittal convexity and an individual insertion angle towards the coronal tangent at the entry point can be established via the tube.

After opening the dura, once the appropriate trajectory is chosen, a ventricular catheter is inserted according to the pre-calculated insertion angle (for a detailed description see Thomale *et al*.
[20]). After receiving tactile feedback from entering the ventricle, the stylet is removedCerebrospinal fluid (CSF) drainage ensures that the ventricular catheter is correctly in place. Catheters deemed to be suboptimally placed are repositioned when necessary. We rely on length markings on the ventricular catheter and, when possible, flow through the distal catheter to ensure the catheter has not been moved after fixation to the skin and is continuing to provide a conduit for CSF. The remainder of any following shunt procedure or connection to an Ommaya reservoir will be performed using standard techniques.

The classical freehand technique uses anatomical landmarks and the catheter is placed in the anterior horn of the lateral ventricle through a burr hole just anterior to the coronal suture in the mid-pupillary line (at the level of Kocher’s point; a point on the surface of the cranium 2.5 cm from the midline and 1 cm anterior to the coronal suture, approximately 11.5 cm above the nasion). The target is the ipsilateral frontal horn just anterior to the foramen of Monro to avoid the choroid plexus. The right nondominant side is preferred. The catheter is directed freehand, using external landmarks in the coronal plane towards the ipsilateral medial canthus and in the sagittal plane through the external auditory meatus. A post-procedural CT scan of the brain is performed within 24 hours as part of standard care for postoperative control, or earlier in case of postoperative CSF drainage problems.

### Mini-tablet application

Regular DICOM viewing software, commonly used in clinics to evaluate radiological imaging, integrates simple measurement tools (such as distance or angle measurements). This technique is used to define a trajectory with an entry point at the frontal paramedian convexity towards the foramen of Monro in a coronal section. Then, measurements can be taken to determine the angle between the trajectory and the respective tangent at the entry point on the skull surface. An iPhone™ (Apple Inc., Cupertino, California, United States) software application is used, importing anonymous imaging material. This image should be a coronal section with the lateral ventricles shown at the level of the anterior commissure. The next step is to define a paramedian entry point on the surface of the skull by tapping the finger on the respective spot. Then, the two feet are virtually placed on the skull surface. A rectangular trajectory orientation of the tube is then shown as a dotted line and can be shifted if necessary. The angle deviation from a rectangular insertion is then given by the software as a value. In addition, the finger may be placed on the target within the ventricle, and the length of the catheter will be given as distance value. As an alternative, the CT scan (at the level: coronal section with the lateral ventricles shown at the level of the anterior commissure) can be photographed and used for angle calculations.

### Outcome assessment

#### Primary outcome measures

The first primary outcome measure will be the frequency and percentage of correct placements of the ventricular catheter, assessed by the three-point scale of Kakarla *et al*., with an additional 1a/1b criteria (Table 
1)
[21]. The effect size will be measured using relative risk, absolute risk reduction, and numbers needed to treat. The second primary outcome measure will be the frequency and percentage of acute ventricular revisions (within one week for an improperly placed catheter). Assessment is performed by an investigator blinded to the study allocation. The effect size will be measured using relative risk, absolute risk reduction, and numbers needed to treat.

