**Methods/Design:**

This is a single center, prospective, randomized trial with a blinded endpoint (ventricular catheter tip location) assessment. Adult patients with the indication for ventriculostomy, as proven by computed tomography (CT), will be randomly assigned to the treatment group or the control group. For patients in the treatment group, ventriculostomy will be performed using an adjustable guiding device and DICOM (Digital Imaging and Communications in Medicine) image-reading software assistance (for example, using a mini-tablet) based on preoperative CT imaging.

Patients in the control group will receive standard freehand ventriculostomy using anatomical landmarks. The catheter may be placed for external drainage or internal (ventriculoperitoneal) shunting in both groups. The primary outcome measure is the rate of correct placements of the ventricular catheter, defined as a score of 1 to 3 on grading system for catheter tip location on a postoperative CT scan. Participants will be followed for the duration of hospital stay, an expected average of two weeks. The primary outcome will be determined by one of the authors blinded to the treatment allocation. We aim to include 236 patients in three years. Secondary outcome measures include: frequency of placements required, frequency of completed placements within the ventricle of the perforated part of the catheter tip, frequency of very early and early shunt failures (revision of the ventricular drainage within 24 hours and within the hospital stay), frequency and percentage of complications (procedure-related and nonsurgical) at discharge.

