### Reporting and statistical analysis

The reporting of this trial will conform to the reporting guidelines outlined in the Consolidated Standards of Reporting Trials (CONSORT) for non-pharmacological interventions statement of 2010
[25]. The statistical analysis will be by the intention-to-treat principle. The occurrence of the primary outcome (number and frequency of correct ventriculostomy) will be compared between the two randomization groups. The secondary outcome analyses will compare the above-described variables between randomization groups. Subgroup analyses will be performed to evaluate whether other parameters such as age, ventricle size, diagnosis, or experience of the surgeon may influence the results. Data are presented as mean and standard deviation or as median with 25/75 percentiles. Stata version 11.2 StataCorp. 2013. *Stata Statistical Software*, College Station, Texas, United States) will be used for all analyses.

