### Interim analyses

This trial will follow a group sequential design, with two stop-points (interim and final analysis; K = 2). The trial will stop if efficacy rules are met. The endpoints assessed at the first stop-point will be based on primary outcomes and adverse events. The first will be the interim analysis which will occur after the accrual of 60 patients in each arm (120 total), thus representing an information fraction of 0.51 at interim analyses. For the efficacy stop-point the commonly used O’Brien-Fleming approach will be used, and a *P* value of 0.0051 at the interim and 0.0415 at the final analysis will be used
[26].

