## Discussion

Studies assessing catheter malplacement find a high percentage of cases of misplacement. Following head trauma, mass lesions, or in slit ventricles, there is a situation of altered anatomy, rendering catheter placement difficult. For example, the ventricles may be compressed and deviated and therefore difficult to cannulate. Furthermore, if the ventricular catheter is placed in the context of a shunt, high revision rates add to patient morbidity and procedural costs. As there is a need to improve current practices in the placement of ventricular catheters, this VENTRI-GUIDE protocol aims to assess if a portable, easy-to-use, mini-tablet-assisted guide for ventriculostomy can increase the accuracy of ventriculostomy in comparison with the freehand pass technique. Our primary outcome is the rate of correct placements of the ventricular catheter, measured using a three-point grading scale for the outcome of each ventriculostomy.

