### Limitations

Simply monitoring of patients and tracking within a study will already improve performance in most cases, and attention to catheter placement will likely have a similar effect
[19]. In addition, this trial is structured to detect a rather large difference in ventricular misplacements. We are seeking an approximate 15% change, from 35 to 20% hit rate, something which may be very difficult to achieve.

A key limitation is the expected to be an imbalance of surgical skill and/or a learning curve. The surgeons who use the freehand technique will be more experienced using the freehand technique than the mini-tablet-assisted method because they will have performed more procedures using freehand, and we may underestimate the effect size of the guide-assisted method.

In addition, we feel that a learning curve is present, but small because of the similarity between the two procedures. Nonetheless, this limitation is common to surgical randomized controlled trials and will be minimized as best as possible within the limitations of our resources, mostly by doing frequent teaching sessions prior to the opening of the trial. The clinical diagnosis might have an impact on the rate of misplacements with highest rates for suboptimal placements in trauma patients with a midline shift on a CT scan
[21], an effect reducible using randomization, as in the present study.

In conclusion, we have developed a protocol to evaluate if an easy-to-use, portable, image-guided system could reduce the need for multiple passes and improve the rate of accurate catheter placement compared to the standard freehand technique. In contrast with earlier studies, this study is prospective, controlled, and randomized. Considering the high revision rates for patients, especially with small ventricular sizes, the guided technique may lead to better outcome and may be cost-effective. Since the outcome of catheter placement is assessed using an established grading system for catheter tip location post-surgery as the primary endpoint, this study will provide an answer for whether an increase of accuracy for ventriculostomy can be reached in patients with guided ventriculostomy.

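### The protocol names two primary outcomes in one section and one everywhere else, so the outcome that governs the efficacy stop is not determined

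*Protocol article*

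**What the plan says.** Primary outcome measures lists two primaries. One is placement: "The first primary outcome measure will be the frequency and percentage of correct placements of the ventricular catheter". The other is revision: "The second primary outcome measure will be the frequency and percentage of acute ventricular revisions (within one week for an improperly placed catheter". The section adds that assessment is by an investigator blinded to allocation.

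Four other places name one primary:
- Abstract, Methods/Design: "The primary outcome measure is the rate of correct placements of the ventricular catheter". The revision outcomes there are secondary and cover other windows: "revision of the ventricular drainage within 24 hours and within the hospital stay".
- Reporting and statistical analysis: "The occurrence of the primary outcome (number and frequency of correct ventriculostomy) will be compared between the two randomization groups".
- Discussion: "Our primary outcome is the rate of correct placements of the ventricular catheter".
- Limitations: "using an established grading system for catheter tip location post-surgery as the primary endpoint".

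Sample size analysis uses placement miss rates only (31%, halved to 15.5%) and reaches 118 per arm. Interim analyses provides for stopping on efficacy after 60 patients per arm, with P thresholds of 0.0051 at the interim and 0.0415 at the end, and says: "The endpoints assessed at the first stop-point will be based on primary outcomes and adverse events".

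**The concern.** The number of primary outcomes depends on which section is read, and the ambiguity carries into the stopping rule. One undivided pair of thresholds is given beside a plural, and the text does not say whether placement alone, either outcome or both must cross. Each answer gives a different trial, with its own false-positive rate, power and meaning for a stop at 120 patients. If the choice were made after data had been seen, the primary result would be open to challenge.

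There is also a question of bias. Blinded grading protects a CT reading of tip location. Revision is different, because the event exists only once someone decides to revise. The treating physician performs the randomization online and the device is used openly in theatre. If the treating team makes that decision, blinded assessment afterwards may not remove bias from it.

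**Working it through.** **1. What the sample size covers.** Inputs from Sample size analysis: p1 = 0.31, p2 = 0.155, two-sided alpha 0.05, power 80%. With mean rate p = 0.2325 and pooled variance under the null:

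n = [1.960·√(2·p·(1−p)) + 0.842·√(p1(1−p1) + p2(1−p2))]² / (p1−p2)²
= [1.960·0.5974 + 0.842·0.5873]² / 0.155²
= 1.6651² / 0.155² = 115.4, so 116 per arm.

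With 30.8% against 15.4% it is 117. The stated 118 is therefore reproduced to within two patients, from placement alone. Power at 118 per arm is 80.9% for a single look at 0.05, and about 79% by binomial simulation at the stated two-look thresholds. No revision rate enters.

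**2. Error spent on one outcome.** P values of 0.0051 and 0.0415 correspond to |Z| limits of 2.80 and 2.04. The information fraction is 120/236 = 0.508, so the two looks correlate at √0.508 = 0.713. The bivariate normal probability of crossing at either look under the null is 0.0436.

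**3. Two outcomes, either one sufficient.** For independent outcomes, 1 − (1 − 0.0436)² = 0.085. For correlated outcomes, by simulation with 2 million replicates at the same thresholds:

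| Correlation between outcomes | Error over both looks | False stop at interim |
|---|---|---|
| One outcome only | 4.4% | 0.5% |
| 0 | 8.5% | 1.0% |
| 0.5 | 7.9% | 1.0% |
| 0.9 | 6.2% | 0.8% |

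**4. Two outcomes, both required.** A false claim needs a false crossing on at least one outcome that has no true effect, so the error cannot exceed the 4.4% of step 2. With no effect on either outcome it is about 0.2% at correlation 0 and 2.5% at 0.9. Power cannot exceed the smaller of the two separate powers.

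**5. Power for revision.** The protocol gives no one-week revision rate, so control rates are assumed. Each is halved in the guided arm, with 118 per arm and the stated thresholds (binomial simulation):

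| Assumed control rate | Guided rate | Power |
|---|---|---|
| 10% | 5% | 29% (28.6%) |
| 20% | 10% | 56% |
| 30% | 15% | 78% |
| 40% | 20% | 91% |

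**The case against.** The best defence is that placement alone was always meant to carry the test. It is the only primary comparison named in the statistical analysis section, and it alone drives the sample size. For revision, the outcome section mentions only effect measures. The interim sentence also lists adverse events, which are plainly not tested at 0.0051, so being listed there does not make an outcome an efficacy trigger. An article may also leave a multiplicity rule to the full protocol or analysis plan. All of this is fair, and the missing rule is not itself the finding. What remains is that the article contradicts itself on the number of primaries and then hangs a stopping decision on the plural. An analysis plan cannot make those sections agree.

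Four stronger readings are tempting, and the documents do not support them.
- **Revision is tested at full alpha.** No significance level is assigned to it. This is an inference from the undivided thresholds, and inflation arises only if either outcome suffices.
- **The error is 9.75%, or 9.1% at correlation 0.5.** Those figures assume a single look at 5% on each outcome, and this design has two looks at lower thresholds. Independence is also unlikely, since revision is defined by improper placement, so the 8.5% is probably an upper end.
- **Revision has no power.** That holds only for low assumed control rates. The Abstract mentions 10 to 40% for revision rates and associated complications, which is not a one-week revision rate, and at the top of that range power is ample.
- **The decision to revise is biased.** The article does not say who decides, or whether improper placement is confirmed blind. The risk is plausible but conditional.

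**Conclusion.** The contradiction stands on the text. One section names two primary outcomes and four places name one, and the efficacy stop has no determined endpoint. The size of the harm depends on a rule the article does not state. Under an either-suffices rule, two-sided error is between 6.2% and 8.5% for correlations from 0.9 down to 0, against 4.4% for one outcome, and a false early stop rises from 0.5% to between 0.8% and 1.0%. The early-stop increase is small in absolute terms; the overall error exceeds 5% throughout that range. Under a both-required rule error is controlled, but power is capped by a revision power that the document does not allow anyone to calculate. Under a placement-only rule there is no statistical harm, but the outcome and interim sections then misdescribe the design. The point should be settled before the interim analysis.

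**What to change.** Name catheter tip location as the sole primary endpoint and as the only endpoint to which 0.0051 and 0.0415 apply. Make one-week revision for improper placement a key secondary outcome, tested only if the primary is significant. Align the Abstract, Primary outcome measures, Reporting and statistical analysis, and Interim analyses. It would also help to state who decides on revision and whether improper placement is judged blind.

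Keep one-week revision separate from the 24-hour and in-hospital revisions under Secondary outcome measures. They overlap, so one event may count in both, but the latter carry no cause restriction, and merging them would change what is estimated.

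The cost is wording. The planned 118 per arm stands, and the small downside is that revision alone can no longer carry a positive trial. If the sponsor prefers to keep two alternative primaries, an equal split (0.025 each, single-look calculation) would need 140 per arm, 280 in total, for placement. At 118 per arm, power for placement would fall from 0.81 to 0.72.
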